### Trial population

The target population in ATLANTIS consists of patients with metastatic or locally advanced UC (T4b and/or N1–3 and/or M1) who are not being considered for radical therapy. Patients must have achieved an objective response or stable disease, according to local radiology review, after 4–8 cycles of first-line chemotherapy. Patients must be able to start maintenance treatment within the study at least 3 but no more than 10 weeks after completion of their first line of chemotherapy for metastatic or locally advanced disease. Biomarker analysis of archival tissue to determine ATLANTIS biomarker-defined subgroups can occur any time after the diagnosis of UC, after appropriate consent has been given.

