### Study objectives and end points

The principal research question is whether molecularly targeted maintenance therapy after chemotherapy can delay the time to progression in molecularly selected patients with advanced UC. ATLANTIS will thereby establish initial evidence of activity for the novel drug/biomarker combinations used in order to justify further phase III validation. A number of drugs will be tested, each compared with placebo or (where this is not feasible) observation alone. Treatment will be allocated on the basis of molecularly defined subgroups of patients (where laboratory/clinical evidence to support such enrichment is clear) or in a manner that allows exploration of, or provides initial evidence for, predictive biomarkers. Of note, it is anticipated that in most cases the biomarker for a particular arm of the trial will itself be experimental and not yet prospectively validated.

The primary end point is PFS. This has been chosen as it is largely objective and the majority of patients with UC display progression in accordance with RECIST 1.1 criteria. PFS is also clinically meaningful as the progression after first-line chemotherapy represents the transition to the lethal stage of the disease and often the requirement for further systemic therapy.

The secondary end points in ATLANTIS are OS, response rate, maximum percentage decrease in measurable disease, safety and tolerability. Exploratory end points are PFS in biomarker-defined subgroups other than those used for selection. Exploratory research hypotheses are embedded in the primary purpose of the trial. As such, all patients must provide adequate tissue for biomarker analysis prior to participation in the trial. This tissue collection will provide a bio-resource for future research relating to UC. The trial also provides a generic umbrella-design framework allowing new drugs to be introduced by amendment in the future. The SPIRIT (Standard Protocol Items: Recommendations for Interventional Trials) figure for ATLANTIS trial is shown in Fig. 2.

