### Trial analysis plan

The design of each ATLANTIS subgroup is based on a randomised phase II screening design to detect a certain level of improvement in PFS with the novel drug compared with matched placebo with 90% power at the 20% one-sided level of statistical significance or equivalently with 80% power at the 10% level of statistical significance. At the end of each subgroup analysis, if the observed PFS difference in favour of the novel agent is statistically significant, this may be a signal that a subsequent phase III trial is warranted. Within each subgroup of ATLANTIS, randomisation (1:1) will be stratified via minimisation factors according to the following: cisplatin versus non-cisplatin primary chemotherapy, Eastern Cooperative Oncology Group (ECOG) score, best response to first-line chemotherapy, progression during the final three months of chemotherapy, presence of visceral metastases, presence of measurable disease at trial entry and investigational site.

The data analysis will be on an intention-to-treat basis within each trial subgroup. PFS will be compared between the novel agent and placebo in each study subgroup within the context of a Cox model incorporating the baseline minimisation factors, based on a randomised phase II screening design to detect improvement in PFS with the novel drug compared with placebo/observation. The *P* value for the observed hazard ratio will be determined from the Cox model in each subgroup. If the observed PFS difference in favour of the novel agent is statistically significant at the 10% one-sided level, this will be deemed a clear signal that a subsequent phase III trial is warranted. A result significant at the 20% one-sided level would require further evidence in terms of improvement, such as reduction in size of measurable disease. A Mann–Whitney *U* test will be used for this comparison. This decision-making process follows a three-outcome-type design. The OS and PFS will be illustrated by using Kaplan–Meier plots. Response rates will be compared within subgroups in the context of a logistic model incorporating minimisation factors. The worst toxicity grades experienced during chemotherapy will be compared by using the Mann–Whitney *U* test.

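### The stated toxicity comparison names the chemotherapy period, which ends before trial treatment starts, so as worded it cannot inform the safety end point

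*Protocol article*

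**What the plan says.** The Trial analysis plan section describes the final analyses within each subgroup. On toxicity it says "The worst toxicity grades experienced during chemotherapy will be compared", by Mann–Whitney U test. The article states no other between-arm analysis of toxicity.

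Safety is a named end point under Study objectives and end points: "The secondary end points in ATLANTIS are OS, response rate, maximum percentage decrease in measurable disease, safety and tolerability".

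The Trial population section sets the order of events. Patients must have shown response or stable disease "after 4–8 cycles of first-line chemotherapy", and must be able to start maintenance "at least 3 but no more than 10 weeks after completion of their first line of chemotherapy for metastatic or locally advanced disease". The research question is "whether molecularly targeted maintenance therapy after chemotherapy can delay the time to progression", and the control is described as follows: "A number of drugs will be tested, each compared with placebo or (where this is not feasible) observation alone".

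**The concern.** A safety comparison has to cover a period in which the arms are treated differently. The period named here is chemotherapy, which every patient has completed before trial treatment begins and which is not a randomised treatment in any subgroup. Worst grade over that period is a baseline characteristic. Comparing it between arms can only show a chance imbalance in patients' histories.

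What is at stake is the formal analysis of one secondary end point. If the sentence were carried out literally, the article's only stated between-arm toxicity test would be uninformative about cabozantinib, rucaparib and enzalutamide alike.

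**Working it through.** The plan gives no figure to reproduce, because the point rests on the period analysed. The check sets the statements side by side.

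1. **Period analysed.** Trial analysis plan: worst grade over the chemotherapy period.
2. **When that period ends.** Trial population: maintenance starts at least 3 and at most 10 weeks after first-line chemotherapy is complete. Chemotherapy-period grades therefore precede the first exposure to trial drug by at least 3 weeks.
3. **Whether the grades also precede randomisation.** The article does not date randomisation explicitly. The eligibility rule needs a disease assessment after 4 to 8 cycles. The minimisation factors include "best response to first-line chemotherapy, progression during the final three months of chemotherapy". Both require the chemotherapy course to be known at allocation. Step 2 is enough even without this inference, since a grade recorded before the first dose cannot be caused by that dose.
4. **Whether chemotherapy could mean the trial drugs.** The article calls them novel agents, trial drug, maintenance therapy or Investigational Medicinal Product, never chemotherapy. Neither arm of any current comparison contains chemotherapy as allocated treatment.
5. **Whether it could mean chemotherapy given after progression.** That would be later in time, but it would record the toxicity of a subsequent treatment, in those patients who received it. It would not measure toxicity of the maintenance drug.

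**Consequence for the test.** Let X be worst grade during chemotherapy. Allocation cannot alter X, so its expected distribution is the same in both arms whatever the drug does:

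P(reject | drug toxic) = P(reject | drug not toxic) ≈ α

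As an illustration, the Mann–Whitney U test was simulated at the planned arm sizes. These follow from the Sample size section with 1:1 allocation: 140/2 = 70 (cabozantinib), 80/2 = 40 (enzalutamide) and 48/2 = 24 (rucaparib). Both arms were drawn from one assumed distribution of grades 0 to 4 (0.10, 0.25, 0.30, 0.25, 0.10), with a two-sided 5% level (also assumed) and 4,000 runs.

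| Patients per arm | Proportion of runs rejecting |
|---|---|
| 70 | 4.8% |
| 40 | 5.2% |
| 24 | 5.0% |

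The Monte Carlo standard error is √(0.05 × 0.95 / 4000) = 0.34 percentage points, so all three agree with 5%. The simulation used simple random draws. The trial uses minimisation on factors such as cisplatin versus non-cisplatin chemotherapy, which could make an unadjusted rank test somewhat conservative for this variable. Either way the rejection rate carries no information about the trial drug.

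**Extent.** The sentence applies within every subgroup: 140 + 48 + 80 = 268 planned patients.

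**The case against.** The strongest reply is that this is a slip of wording and not a choice of analysis. Safety and tolerability are end points of a maintenance trial. The independent data monitoring committee (IDMC) reviews toxicity alongside treatment delivery and compliance, which are on-trial data. Nothing in the article gives a reason to compare chemotherapy histories. That is very probably right, and it limits the point to a correction of wording. It does not remove the point, because the sentence names a period, the period is wrong, and no other statement in the article puts it right.

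A second reply is that the full protocol or SAP may name the correct period. That cannot be seen here. The point concerns a period that the article states wrongly, not detail left to another document.

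A reader might infer two stronger things that the article does not support:

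- **That a toxic agent could pass to phase III because of this sentence.** The signal rule in the Trial analysis plan uses PFS at the 10% or 20% one-sided level, with further evidence such as reduction in measurable disease at the 20% level. The toxicity test is not part of that rule, so its wording does not change the signal.
- **That safety goes uncollected or unmonitored.** The same section has the IDMC review study data roughly annually, including toxicity, and base its recommendations on all available data. That review gives no between-arm test or period for the final analysis, so it does not replace the secondary analysis, but it does mean that patients are monitored.

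Nor is it a finding that the article omits the safety population, the end of the reporting window or the handling of baseline grade. An article commonly leaves these to the full protocol or SAP.

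**Conclusion.** The point holds as an error in a stated analysis. As worded, the only between-arm toxicity comparison in the article is made on a variable fixed before trial treatment, so it cannot inform safety and tolerability in any of the three subgroups. Its ability to detect drug toxicity is nil: the rejection rate stays at about the nominal level whatever the drug does.

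The reach is limited to one secondary analysis. The primary end point, event targets, significance levels, phase III signal rule and IDMC review are unaffected. The conclusion rests on reading chemotherapy as the first-line course, which is its use elsewhere in the trial's eligibility and minimisation rules. The alternative of later chemotherapy would not rescue the sentence. How much it matters in practice depends on whether the operative protocol and SAP carry the same phrase, which is not known.

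**What to change.** In the Trial analysis plan, replace the reference to chemotherapy in the toxicity sentence with trial treatment. Define this as worst grade from the start of allocated maintenance treatment, or from randomisation where the control is observation, over the same reporting period in both arms. The provision for observation is needed because the article allows a control without placebo, and a rule based only on a first dose of trial drug or placebo would leave that control arm without a start point. The Mann–Whitney U test can stay.

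Then check the full protocol and SAP for the same phrase and correct it there if present. The analysis population, the end of the window and the treatment of baseline grade can be settled in those documents.

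The cost is one phrase and a cross-check. Sample size, visits and the analysis method do not change.

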### Sample size

Patients within the cabozantinib subgroup will be randomly assigned to cabozantinib/placebo in a 1:1 ratio. The median PFS on the placebo arm is estimated to be 6 months. The comparison between arms is designed to detect an improvement in median PFS of 9 months with cabozantinib, which corresponds to a hazard ratio of 0.67. This is appropriate for a new agent within an untargeted population and requires 114 PFS events, so recruitment to this subgroup will incorporate 140 patients over about 24 months. This target provides more than 90% power (10% one-sided) to detect between the study arms a difference in reduction of measurable disease corresponding to a standardised effect size of 0.5. Patients allocated to the rucaparib subgroup will be randomly assigned to rucaparib/placebo in a 1:1 ratio. A hazard ratio for this subgroup of 0.5 is targeted on the basis of the striking effect seen with PARP inhibitors in a similar setting with ovarian cancer using HRD biomarker for patient selection. This requires 39 PFS events, which can be obtained by recruiting 48 patients. This recruitment number also provides more than 80% power (10% one-sided) to detect a difference of reduction in size of measurable disease corresponding to standardised effect size of 0.7.

Patients allocated to the enzalutamide subgroup will be randomly assigned to enzalutamide/placebo in a 1:1 ratio. The median PFS on the placebo arm is estimated to be 4 months. The comparison between arms is designed to detect an improvement in median PFS of 6.7 months with enzalutamide, corresponding to a hazard ratio of 0.6. This size of difference is appropriate in a targeted agent in the target population. This requires 72 PFS events, so recruitment to this subgroup will incorporate 80 patients. This number also provides 90% power (10% one-sided) to detect between the arms a difference in the reduction in size of measurable disease corresponding to standardised effect size of 0.65.

## Discussion

Recent studies of second-line therapy, particularly immune checkpoint inhibitors, in patients with UC have demonstrated a clinical benefit for a small proportion of patients. The emerging treatment landscape of UC is also increasingly incorporating these therapies in first-line clinical trials. However, there remains a need to improve outcomes for patients with this challenging disease. ATLANTIS offers a novel approach to previous studies in this arena by offering biomarker-defined selection of maintenance therapy after chemotherapy in patients with UC. The primary research question of this signal-searching multi-arm phase II study is whether targeted maintenance therapy after chemotherapy can delay the time to progression in molecularly selected patients with UC. This would establish clinically relevant evidence of activity in molecularly defined subgroups for the novel drug used. The study design will investigate cabozantinib, enzalutamide and rucaparib in this setting but also provide a generic framework that will allow new treatments to be introduced into the study in the future with prospective stratification based on a molecular target.

At present, there are no targeted therapies with proven activity in UC. Pre-clinical data suggest that there are a number of eligible targets, but the number of randomised trials performed to test these hypotheses has been small. The reasons behind this remain unclear, but low levels of clinical activity in unselected patients with UC in non-randomised phase II trials do not support progression to phase III trials. Another explanation is that the combination of targeted therapy and standard chemotherapy is poorly tolerated in this patient population. ATLANTIS will be a leading global study in the development of personalised targeted therapy for patients with UC.

Such a positive randomised phase II study would be a significant breakthrough in UC and may lead to randomised phase III trials in both the metastatic and adjuvant setting. If a cohort of ATLANTIS is positive, it would be anticipated to lead to a randomised phase III study of maintenance therapy in the appropriately selected UC population. There is also an unmet need for adjuvant therapy in patients with high-risk muscle invasive bladder cancer, and a positive signal from ATLANTIS would also support a randomised phase III trial in this patient group with appropriate molecular selection.

Patients in ATLANTIS are asked to consent to the collection of surplus tissue for translational research. Translational research hypotheses are embedded in the primary purpose of this trial, the aim of which is to demonstrate efficacy of predictive and appropriate drug interventions in UC. As such, all patients must provide adequate tissue for biomarker expression prior to trial participation. This will also provide a bio-resource for future research in UC.

The ATLANTIS trial reflects an exciting innovation in front-line precision cancer medicine for patients with advanced UC. The study design, with a biomarker-negative arm, allows all patients who enter pre-screening to potentially be able to take part. The adaptive design also allows maximal opportunity to detect an efficacy signal and rapid inclusion of new hypotheses. The engrained translational research components have the potential to resolve some of the unanswered questions and push new frontiers in the management of this challenging disease.

## Trial status

At the time of publication, ATLANTIS was open to recruitment across 32 UK cancer centres. Trial recruitment began in November 2016, and the estimated first subgroup recruitment end date is December 2020. The current ATLANTIS protocol is version 2.4 (21 June 2019).

## Data Availability

Not applicable.

## Abbreviations

AR: Androgen receptor
BAP1: BRCA-1 associated protein-1
BRCA: Breast cancer susceptibility protein
ERCC2: Excision repair cross-complementation group-2
FANCD2: Fanconi anaemia group D2 protein
HRD: Homologous recombination deficiency
IDMC: Independent data monitoring committee
LOH: Loss of heterozygosity
MET: MET proto-oncogene
OS: Overall survival
PALB2: Partner and localizer of BRCA2
PARP: Poly (ADP-ribose) polymerase
PFS: Progression-free survival
UC: Urothelial cancer
VEGF: Vascular endothelial growth factor
